### Outcomes

The primary outcome is dengue incidence rates in communities (
Table 2)

**Table 2. T2:** Primary and secondary outcome measures and other outcomes. Baseline is June when school starts in Myanmar. (Y1=Year 1, Y2=Year 2).

Outcome	No.	Name	Index	Description	Unit	Frequency of data collection	Details
Primary outcome	1	Dengue incidence rate in communities	DI	Confirmed number of dengue cases (numerator) and the estimated population in each school catchment area (denominator) during study period	No. cases during study period / population	Continuous	Passive case detection assessed using dengue rapid diagnosis tests (RDT) in public hospitals and health centers
Secondary outcomes	2	Seroconversion rates in school children	SR _S_	Seroconversion rates between two time points in students at school	No. of seroconversions / no. observation-days	3 times: - Jun. Year 1 (baseline), - Oct. Year 1, - Feb. Year 2.	Seroconversion rates assessed by dengue rapid diagnosis tests (RDT)
	3	Seroconversion rates in households	SR _H_	Seroconversion rates between two time points in 20 households in communities	No. of seroconversions / no. observation-days	3 times: - Jun. Year 1 (baseline), - Oct. Year 1, - Feb. Year 2.	Seroconversion rates assessed by dengue rapid diagnosis tests (RDT)
	4	Mosquito adult index in schools	AI _S_	Mean number of adult female *Ae.* *aegypti* and *Ae. albopictus* per school collected indoors and outdoors	No. / school	4 times: - Jun. Year 1 (baseline), - Oct. Year 1, - Feb. Year 2, - Jun. Year 2.	Mosquito collections using a battery- driven mechanical aspirator.
	5	Mosquito adult index in households	AI _H_	Number of adult female *Ae. aegypti* and *Ae. albopictus* per school or house collected indoors and outdoors	No. / household	4 times: - Jun. Year 1 (baseline), - Oct. Year 1, - Feb. Year 2, - Jun. Year 2.	Mosquito collections using a battery- driven mechanical aspirator.
	6	Breteau index in schools	BI _S_	No. of *Aedes* positive containers per 100 schools	No. / 100 schools	4 times: - Jun. Year 1 (baseline), - Oct. Year 1, - Feb. Year 2, - Jun. Year 2.	Mosquito collections in schools
	7	Breteau index in households	BI _H_	No. of *Aedes* positive containers per 100 houses	No. / 100 houses	4 times: - Jun. Year 1 (baseline), - Oct. Year 1, - Feb. Year 2, - Jun. Year 2.	Mosquito collections in households

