### Sample size

The required sample size was estimated based on the primary outcome, dengue incidence in communities. Since the numbers of dengue cases in each school catchment area were unknown, the sample size is necessarily an estimate. This estimate was attained by using township level data from the two selected study townships. There was a total of 2,885 dengue cases in South Dagon and Shwepyithar townships during 2013–2018 giving an average of 480 cases/year during this period. Dividing the number of cases with the number of middle and high schools in these two townships gives a conservative estimate of 480/46=10.5 cases per school catchment area per year. We plan to recruit a minimum of about 40 students per school per year. The calculations would assume that in the control, the incidence is 10.5 dengue cases per 40 person-years of observation i.e., incidence rate of 0.26 dengue cases per person-year of observation and expect this to drop to approximately 0.18 dengue cases per person-year of observation in the intervention (i.e., 7.35 dengue cases per 40 person-years of observation). Using a cluster randomized design with 46 schools (23 schools per arm) and 10.5 cases per school catchment area at baseline, with α=0.05 this study has more than 80% power to detect an approximate 30% reduction in the dengue incidence rates between the control and the intervention arms. This estimate assumed an intra-cluster correlation coefficient (ICC) of 0.01. An intra-cluster correlation coefficient (ICC) for the dengue outcome is not available in the literature. We therefore used the next best available estimates, based on our previous assessment of ICCs for malaria prevalence and incidence in Myanmar which are low in this country, on average 0.003 (95% CI 0.000-0.010)
^
45
^. Although malaria is a different vector-borne disease with different transmission pattens in different settings, we think that the ICCs for malaria in Myanmar probably are the most realistic we can get and provide better estimates than unfounded guesses. The ICC is context-specific (location, spatial scale, etc.) and is preferred for studies with binary outcomes, such as this trial. As an additional guide, a reduction in dengue incidence by 25–30% would be consistent with the objectives of both the WHO Global Strategy for dengue prevention and control 2012–2020
^
46
^ and the WHO Global Vector Control Response 2017–2030
^
37

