**Figure 2. f2:**
[figure not shown]
Time schedule of enrolment, interventions, and pre- and post-allocation data collections based on Standard Protocol Items: Recommendations for Interventional Trials (SPIRIT) checklist
^
48
^. Arrows indicate continuous activities. Dashed arrow indicates that some of the vector control interventions will continue until June Year 2. Primary and secondary outcome measures in parentheses; see
Table 2 for further details.

The secondary disease outcomes will be assessed by seroprevalence assessments in schools and households at baseline (June Year 1) and at two follow-ups (four and eight months after baseline) and seroconversions between these two time points. In each school, a total of 40 students, teachers and staff (20 randomly selected 6
^th^ grade students, 20 randomly selected students in grade 1–5 based on feasibility and financial reasons) will be asked to provide a finger prick blood sample for a dengue RDT. Similarly, seroprevalence will be assessed in 40 households per school catchment area of which 20 will be students’ households and 20 randomly selected households in each school catchment area. One randomly selected person (any age >1 year old) in each household will be selected. Thus, there will be 20*23 = 460 individuals in each group (6 graders, grades 1–5, student households and other households) which permits detection of a 30% difference in seroconversion between the two study arms allowing for a 10% dropout rate, with 80% power and 5% significance. The presence of dengue antibodies (IgG and IgM) will be confirmed by a finger prick blood sample of 10μL and a rapid diagnosis test (RDT) kit (SD BIOLINE Dengue IgG/IgM, Standard Diagnostic Inc., Korea). A seroconversion will be determined when an RDT negative person becomes positive in a subsequent collection. Written informed consent will be taken. Data on potential confounders, e.g., age, sex, residence, travel history, and previous dengue history will be collected for each person using a short case report form (CRF).

**
*Mosquito collections.*

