^. For the primary analysis, missing data may occur if complete clusters decline to continue in the trial. In this case, the cluster will still be included as long as any data on the primary outcome are available. This does introduce a risk of bias in estimating effectiveness, if loss of clusters is related to performance of the interventions. Dengue incidence in communities will be analyzed using a Poisson regression model. A negative binomial regression will be considered if there will be over-dispersion in the Poisson distribution. The response variable will be the number of dengue cases per cluster and the exposure will be the person-time at risk. Hence, the analysis will yield rate ratios. Multilevel models will not be used for this outcome since the number of cases may be too small for them to be fitted robustly. Statistical significance will be declared at 5% significance level. The 95% confidence intervals will be calculated and reported where applicable. A detailed statistical analysis plan (SAP) will be developed prior to database lock.

**
*Effect of intervention on secondary outcomes*
**

2. 
**Seroconversion rates in schools (SR
_S_).** The proportion of dengue antibody seroconversion in schools will be calculated as the number of seroconversions between the baseline and subsequent follow-ups at four and eight months after the implementation of the interventions divided by observation-days of school populations. The definition of seroconversion is when a participant has converted from being IgG (or IgM) negative during one sampling event to being IgG (or IgM) positive during a second sampling event. Dengue incidence based on seroconversions will be analyzed using a Poisson regression model. A negative binomial regression will be considered if there will be over-dispersion in the Poisson distribution. The response variable will be the number of dengue cases per cluster and the exposure will be the person-time at risk. Hence, the analysis will yield rate ratios. Multilevel models will not be used for this outcome since the number of cases may be too small for them to be fitted robustly.3. 
**Seroconversion rates in households (SR
_H_).** The proportion of dengue antibody seroconversion incidence in a selection of 40 households per school catchment area will be calculated and analyzed in the same way as for schools.4. 
**Mosquito Adult Index in schools (AI
_S_).** This the number of adult female
*Ae. aegypti* and

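### The stated 80% power for seroconversion with 460 people per group is not supported by the clustered, eight-month design, and the unit it refers to is unclear

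*Protocol article*

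**What the plan says.** The power statement for serology is in Data collection, under Disease surveillance. Four groups are sampled: sixth graders, grades 1–5, students' households and other households. For these, "Thus, there will be 20*23 = 460 individuals in each group", "which permits detection of a 30% difference in seroconversion between the two study arms allowing for a 10% dropout rate, with 80% power", at 5% significance. Since 23 is the number of schools per arm, 460 is per group per arm. Dropout is the only allowance named. Surveys take place at baseline, four months and eight months, and a seroconversion is counted when someone RDT-negative later turns positive.

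The Sample size section, for the primary outcome only, gives a control "incidence rate of 0.26 dengue cases per person-year of observation" and says the authors "expect this to drop to approximately 0.18 dengue cases per person-year of observation in the intervention". It adds: "This estimate assumed an intra-cluster correlation coefficient (ICC) of 0.01". The malaria ICC cited there averages 0.003, with 0.010 as its upper confidence limit.

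On the household sample, Table 2 describes outcome 3 as "Seroconversion rates between two time points in 20 households in communities". Data collection describes 40 households per catchment area (20 of students, 20 others), and Data analyses computes the outcome "in a selection of 40 households per school catchment area". Data analyses also treats school seroconversion as one outcome, and defines conversion by IgG or IgM turning from negative to positive.

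**The concern.** A power figure for a cluster trial should reflect the clusters, the length of follow-up and the number of people who can have the event. This one shows none of these, although all three are features of the protocol's own serology design. If it was computed as though individuals were randomised, followed for a full year and all at risk, it is too high for the inputs used.

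What is at stake is interpretation. The Discussion concedes that asymptomatic infections do not reach clinics, so the passively detected primary outcome misses them, whereas seroconversion can capture them. A null seroconversion result read against a nominal 80% power could be taken as evidence of no effect on transmission. The article also offers itself as a basis for future implementation, so the figure may be reused.

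The household count adds a separate problem. With 20 in one place and 40 in two others, it is unclear whether the stated power belongs to any analysis that will be run.

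**Working it through.** **Inputs.** 460 per group per arm in 23 clusters of 20; 10% dropout; 5% significance (two-sided assumed); surveys to eight months (Data collection). Rates of 0.26 and 0.18 per person-year and ICC 0.01 or 0.003 (Sample size, primary outcome; their use for serology is an assumption). The seronegative share is not given; 100%, 70% and 50% are assumed for illustration. The 30% is read as relative.

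**Step 1: reproduce the stated figure.** Unclustered two-proportion formula, with p̄ the mean of p1 and p2:

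n = [1.96·√(2p̄(1−p̄)) + 0.8416·√(p1(1−p1)+p2(1−p2))]² / (p1−p2)²

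With p1 = 0.26, p2 = 0.18, p̄ = 0.22: (1.148 + 0.491)² / 0.08² = 2.686 / 0.0064 = 420 per arm. Dropout: 420/0.9 = 467, or 420 × 1.1 = 462. Conversely, 460 × 0.9 = 414 evaluable gives power Φ[(0.08·√414 − 1.148)/0.583] = 79.5%. Both 460 and 80% are recovered with no design effect, 12 months of risk and everyone at risk.

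**Step 2: clustering only.** 414/23 = 18 evaluable per cluster; design effect (DE) = 1 + (18 − 1) × ICC.
- ICC 0.01: DE 1.17, effective n = 414/1.17 = 354, power 73%.
- ICC 0.003: DE 1.051, effective n = 394, power 77.5%.

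**Step 3: add eight months (ICC 0.01, all seronegative).** This assumes constant risk over the year.
- Rates scaled linearly: 0.26 × 8/12 = 0.173 and 0.18 × 8/12 = 0.120; power 52%.
- Control risk 1 − exp(−0.26 × 8/12) = 0.159 and a risk 30% lower, 0.111; power 46%.

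**Step 4: add people already seropositive (assumed shares).**
- 70% seronegative: 414 × 0.7 = 290, 12.6 per cluster, DE 1.116; power 40% (linear) or 36% (exponential).
- 50% seronegative: 207, 9 per cluster, DE 1.08; power 31% or 28%.

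**Step 5: the control risk that would give 80%.** Solve for the eight-month control risk p among seronegatives, with p2 = 0.7p and ICC 0.01. Pooling both groups gives 2 × 414 = 828 evaluable per arm, 36 per cluster, DE 1.35 if all are seronegative.

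| Seronegative share | One group (20 per cluster) | Two groups pooled (40 per cluster) |
|---|---|---|
| 100% | about 31% | about 20% |
| 70% | about 38% | about 25% |
| 50% | about 47% | about 31% |

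**Step 6: the sampling unit.** Table 2 gives 20 households; Data collection and Data analyses give 40. Power is stated for a group of 20 per cluster, while the analysis text describes one household outcome from 40 and one school outcome. The two columns above show how much this choice matters.

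**The case against.** A reader might infer that 460 per group fails to deliver 80% power, with true power near 45% or lower. The documents do not support that, for these reasons:

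- The power sentence gives neither a control risk nor an ICC, so it does not exclude a design effect. The link to 0.26 and 0.18 is back-fitted, and other inputs also give 80%, as Step 5 shows.
- The 0.26 is a rate of clinical cases stated for the primary outcome. Seroconversion also captures silent infection, and the protocol gives no seroconversion rate. The 46% to 52% depends on a borrowed rate.
- Scaling by 8/12 assumes even risk over the year. The Discussion stresses strong temporal variation, and the share of yearly transmission falling between June and February is not stated.
- It is tempting to say that people positive at baseline cannot convert. Data collection reads that way, but the IgG-or-IgM wording in Data analyses could let someone who is IgG-positive and IgM-negative convert on IgM.
- Clustering alone costs only about 2 to 7 points.
- If the two groups of 20 are pooled, 80% is reached at a control risk of about 20%.

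All of this stands as a limit on the size of the shortfall. It does not rescue the sentence, because no stated assumption justifies 80% for this design. Nor can the point be left to a later analysis plan, because the protocol itself asserts the figure.

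**Conclusion.** The 80% power for seroconversion is unsupported as written. It coincides with a calculation for individually randomised people, all seronegative and followed for a year. On those same rates, clustering brings it to 73% (ICC 0.01) or 77.5% (ICC 0.003). With even risk over eight months as well, it is about 46% to 52% with everyone seronegative, and lower if baseline positives are not at risk. These figures depend on the borrowed primary-outcome rates and ICC and on reading 30% as relative.

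The claim would hold at ICC 0.01 if the eight-month control risk among seronegatives were about 31% to 47% per group, or about 20% to 31% with pooling, over seronegative shares from 100% down to 50%. The protocol asserts no such risk. The 20-versus-40 household conflict is a contradiction that needs no assumption. These are secondary outcomes, and the primary sample size is unaffected. The point should be fixed, but does not threaten the trial's main comparison.

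**What to change.** Replace the power sentence with a range of power or detectable difference that states:

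- the assumed eight-month control risk among seronegatives and its source;
- the assumed seronegative share;
- the ICC and the resulting design effect;
- that 30% is a relative reduction;
- the unit analysed, either each group of 20 per cluster or the pooled 40.

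Make Table 2, Data collection and Data analyses agree on 20 or 40 households. Use one definition of seroconversion in Data collection and Data analyses, saying which marker or markers count and whether someone positive on one marker at baseline remains at risk on the other.

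The cost is a short recalculation, one table correction and aligned wording. No extra participants or visits are needed.

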### Data management

Unique identification numbers will be given to each participating school, teacher, student, and household. Each household member will also receive a project ID number. Data will generally be collected using pre-programmed tablets. A detailed Data Management Plan (DMP) has been developed using ‘FAIR’ principles for Horizon 2020 projects (i.e., data are Findable, Accessible, Interoperable and Re-usable)
^
63
^. Data will be stored in a password protected, anonymized database, which will only be accessible by the study team. Any documentation containing information about patients or biological specimens will be kept in a locked cupboard at the Malaria Consortium office in Yangon. Automated data quality checks will be built into the data collection system with further checks at the time of data extraction and analysis. Spatial data on household locations, mosquito collection sites, and climate will be stored in a spatial geodatabase. This will be supported by a project data manager based in Yangon and supported by the MORU Clinical Trials Support Group and Epidemiology Departments in Bangkok.

### Data monitoring committee

The formation of a data monitoring committee was assessed not to be required, because the trial is considered low risk for participants and of short duration. For the same reasons interim analyses and stopping guidelines were not included in the study.

### Adverse events monitoring and reporting (harms)

No enhanced risks are expected for the participants in this project, whether physical, mental, or social. There is no compensation for study participants (including expenses and access to medical care).

The proposed interventions are environmentally friendly and do not include drugs, vaccines, insecticides, or other chemical substances. Certified nurses, doctors, technicians, or trained project staff will used single-use sterile safety lancets to take blood samples from participants. These lancets are designed to minimize pain during blood sampling and reduce the risk of needle injury by immediate retraction of the needle after use. The interventions are therefore considered safe for humans and have no negative consequences for the external environment. International concerns have been raised whether release of guppy fish might escape into the environment and negatively affect native biodiversity
^
64
^. In this project, guppies will be distributed to isolated water storage containers and are not likely to escape into the environment. There are few, if any, studies showing that the risk of guppy escape into local ecosystems as a result of vector control is high and detrimental to aquatic ecosystems. Furthermore, the National Guidelines for Dengue Prevention and Control in Myanmar recommend the use of larvivorous fish as a dengue larvae control strategy
^
65
^.

### Auditing

There will be no formal auditing of this trial.

### Data analyses

**
*Effect of intervention on primary outcome*
**

1. 
**Dengue incidence rate in communities (DI).** The total cumulative number of dengue cases in the communities will be recorded passively through patients presenting at collaborating public hospitals and health centers in the two townships. Each case will be confirmed by dengue antigen/antibody RDTs. Each case that resides in the school catchment areas will be noted as such. The denominator will be the estimated population in each school catchment area. Data analysis for the primary outcome will be a comparison of the overall difference in incidence rate of confirmed dengue cases between the intervention and non-intervention school catchment areas with sub-analyses comparing the monthly incidence over time, before, during and after the interventions to examine the timing of any intervention impact. Incidence data will be collected continuously over a one-year period. At the cluster level, analysis will be by intention to treat, i.e., taking the trial arm as that to which, each cluster was randomized. At the individual level, people will be taken to have the allocation of the arm in which they are resident at the time of any data contributed. A flowchart showing numbers of clusters, and average numbers of households per cluster, over time will be constructed in accordance with Consolidated Standards of Reporting Trials (CONSORT) guidelines
^
66
^. For the primary analysis, missing data may occur if complete clusters decline to continue in the trial. In this case, the cluster will still be included as long as any data on the primary outcome are available. This does introduce a risk of bias in estimating effectiveness, if loss of clusters is related to performance of the interventions. Dengue incidence in communities will be analyzed using a Poisson regression model. A negative binomial regression will be considered if there will be over-dispersion in the Poisson distribution. The response variable will be the number of dengue cases per cluster and the exposure will be the person-time at risk. Hence, the analysis will yield rate ratios. Multilevel models will not be used for this outcome since the number of cases may be too small for them to be fitted robustly. Statistical significance will be declared at 5% significance level. The 95% confidence intervals will be calculated and reported where applicable. A detailed statistical analysis plan (SAP) will be developed prior to database lock.

**
*Effect of intervention on secondary outcomes*
**

2. 
**Seroconversion rates in schools (SR
_S_).** The proportion of dengue antibody seroconversion in schools will be calculated as the number of seroconversions between the baseline and subsequent follow-ups at four and eight months after the implementation of the interventions divided by observation-days of school populations. The definition of seroconversion is when a participant has converted from being IgG (or IgM) negative during one sampling event to being IgG (or IgM) positive during a second sampling event. Dengue incidence based on seroconversions will be analyzed using a Poisson regression model. A negative binomial regression will be considered if there will be over-dispersion in the Poisson distribution. The response variable will be the number of dengue cases per cluster and the exposure will be the person-time at risk. Hence, the analysis will yield rate ratios. Multilevel models will not be used for this outcome since the number of cases may be too small for them to be fitted robustly.3. 
**Seroconversion rates in households (SR
_H_).** The proportion of dengue antibody seroconversion incidence in a selection of 40 households per school catchment area will be calculated and analyzed in the same way as for schools.4. 
**Mosquito Adult Index in schools (AI
_S_).** This the number of adult female
*Ae. aegypti* and
*Ae. albopictus* (combined) per school or per house collected both indoors and outdoors for 15 minutes at each location (30 min total collection time) using a battery-driven mechanical aspirator. Collections will occur at baseline and once every four months in all schools. A negative binomial regression will be done with the number of mosquitoes as the outcome variable and number of school-visits as the exposure (denominator) variable, i.e., the logarithm of the number of schools as the ‘offset’. A logarithmic link function will be used. Hence, the exponential of the coefficient for arm will be the between-arm ratio in Adult Index (AI) according to the response variable used. Additional analyses of the AI
_S_ will be done by including the baseline value as an additional covariate. Due to the potential skewness of these values, this will be done by categorizing the index as zero, or above or below the median of the positive values.5. 
**Mosquito Adult Index in households (AI
_H_).** This is the same as AI
_S_ except that collections in households will be done for 10 minutes indoors and outdoors, respectively (20 min total collection time). Collections will occur at baseline and once every four months in five selected households per cluster. This index will be calculated and analyzed in the same way as AI
_S_.6. 
**Breteau Index in schools (BI
_S_).** The BI is the number of containers with
*Aedes* immatures/100 schools. It will be calculated at baseline as well as for each of the three follow up time points. This index will be analyzed similarly to the Adult Index.7. 
**Breteau Index in households (BI
_H_).** This BI is the number of containers with
*Aedes* immatures/100 houses. It will be calculated at baseline as well as for each of the three follow up time points. This index will be analyzed similarly to the Adult Index.8. 
**Knowledge, attitudes and practice scores in students (KAP
_S_).** These are based on sum scores on a scale from 1–10, where ten indicates the highest score. Scores will be calculated at baseline and at each of the three follow up time points. The total score for each of the three KAP components will be added, and the resulting value expressed on a scale from 0 to 10. The average KAP scores for each school will be calculated over all surveys done in the intervention period. These school-level averages will serve as the response variable for a statistical analysis using linear regression. The explanatory variable will be whether or not the school received the intervention.9. 
**Knowledge, attitudes and practice scores in parents (KAP
_H_).** These scores will be calculated at baseline as well as for each of the follow up time points and analyzed in the same way as explained above.10. 
**Behavioral assessments (BA
_S_ and BA
_H_).** A behavioral model will be developed based on the latent variables collected through the survey and validated with structural equation modeling. The model will be evaluated, and a model fit determined, using the following indices: the Comparative Fit Index (CFI) and the Tucker Lewis Index (TLI) (CFI/TLI > 0.90), the Root Mean Square of Approximation (RMSEA) (<0.08) and the Standard Root Mean Square Residual (SRMR) (<0.10)
^
67
^. Two multi-group analyses will be performed using two control variables: control vs. intervention arm and pre- vs. post- intervention. To do so, measurement invariance will be tested and compared through Chen’s cut-off points for the Comparative Fit Index (CFI) and McDonald’s Non-Centrality Index (NCI)
^
68
^. To test change in fit between nested models suggested thresholds of 0.005 for ΔCFI and 0.010 for ΔNCI will be used11. 
**Engagement assessment with students (E
_S_).** The photovoice sub-study contribute to developing an understanding of students’ degree of engagement and perceptions and experiences of being a participant in the intervention through photographs as well as qualitative data including photo discussion sessions. The approach to data analysis will be inductive and include thematic analysis of the transcribed photo discussion sessions involving the students as co-researchers through member checking of the code book to ensure inter-coder reliability. This process is often used to assess the trustworthiness of qualitative research findings
^
69
^.12. 
**Engagement assessment with parents and teachers (E
_PT_).** The degree of engagement in interventions in parents and teachers will be assessed using qualitative methods. The approach to data analysis will combine inductive and deductive elements, using determinants and typologies of community engagement
^
70,
71
^. Analytical categories will be developed from the initial research questions and also emerge during the analysis process. Using NVivo, identified categories will be operationalized as codes in a flexible coding scheme. The content of the codes will be discussed extensively between independent coders, and subsequently used to develop themes and to explore patterns.

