^. Lack of data on adult mosquitoes in the study area precluded a sample size calculation for the quantitative secondary outcomes on adult mosquitoes. However, the number of adult mosquitoes in the area is expected to be large
^
47
^, thus giving substantial power to detect differences between the two arms. All 46 schools will be included in the study, using an equal cluster size of 23 schools per arm. Both arms (intervention and control) will be represented in each township. The power calculations were performed in Stata 16.

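### The default primary analysis is a plain Poisson regression with no between-cluster variance, and the move to an over-dispersed model is optional and decided on the data

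*Protocol article*

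**What the plan says.** For the primary outcome, Data analyses states: "Dengue incidence in communities will be analyzed using a Poisson regression model". The unit is the cluster: "The response variable will be the number of dengue cases per cluster and the exposure will be the person-time at risk". The one provision for extra variation is: "A negative binomial regression will be considered if there will be over-dispersion in the Poisson distribution". No test, threshold or timing goes with it. Random cluster effects are ruled out: "Multilevel models will not be used for this outcome since the number of cases may be too small for them to be fitted robustly". The level is fixed: "Statistical significance will be declared at 5% significance level". The same Poisson wording is repeated for seroconversion in schools (SR_S), and seroconversion in households (SR_H) is to be analysed in the same way.

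Elsewhere the protocol expects clusters to differ. Under Sample size: "This estimate assumed an intra-cluster correlation coefficient (ICC) of 0.01". The Discussion describes marked variation of dengue in space and time. For the mosquito indices, Data analyses fixes negative binomial regression outright. Randomization and blinding states that participants and data collectors are not blinded. A detailed SAP is promised before database lock.

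**The concern.** Analysing one count per cluster does not by itself deal with clustering. A Poisson model with arm and a person-time offset has the same likelihood for the arm effect as individual-level Poisson data analysed as if there were no clusters. Its standard error comes only from the total number of cases in each arm. If true rates differ between catchment areas, that standard error is too small, the 95% interval too narrow and the test too liberal.

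Protection then depends on someone noticing over-dispersion and deciding to change model. As written, this is an option and not a rule, and it would be exercised on the data of an unblinded trial. At stake are the level of the primary test and the freedom to choose between two p-values.

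**Working it through.** **Inputs.** 23 clusters per arm (Sample size: "All 46 schools will be included in the study, using an equal cluster size of 23 schools per arm"). Study setting mentions 40 schools, but Sample size and Randomization both use 46, which is used here. Cases per cluster: 2,885 / 6 years / 46 = 10.45 (the protocol rounds to 10.5). Design rates 0.26 and 0.18 per person-year on 40 person-years per cluster, and ICC 0.01 (Sample size). Two-sided 5% is assumed.

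**The plan's own figure.** Sample size claims "with α=0.05 this study has more than 80% power to detect an approximate 30% reduction in the dengue incidence rates". With design effect 1 + 39 × 0.01 = 1.39:
- SE of the log rate ratio = √[1.39 × (1/(920 × 0.26) + 1/(920 × 0.18))] = 0.119.
- |ln(0.18/0.26)| = 0.368, and 0.368/0.119 − 1.96 = 1.13, which gives power of 87%.

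The claim reproduces. It was also checked as two proportions (94%) and with the Hayes-Bennett cluster-rate formula (89 to 90%). Without the design effect the log rate ratio gives 95%. So clustering can enter the sample size, while the default analysis has no term for it.

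**What k might be.** The documents state no k. Two conversions of the design ICC give very different answers:
- 40-person basis: k = √(0.01 × 0.74/0.26) = 0.17.
- Catchment basis: (307,000 + 287,000)/46 = 12,913 people, rate 10.45/12,913 = 0.00081, so k = √(0.01 × 0.99919/0.00081) ≈ 3.5.

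The ICC therefore does not settle k for the outcome actually analysed, and the values below are assumptions.

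**If Poisson is kept.** Variance relative to Poisson = 1 + 10.45k². Type I error = 2 × [1 − Φ(1.96/√(1 + 10.45k²))].

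| k (assumed) | Variance ratio | Type I error, formula | Type I error, simulated | 5% dispersion test triggers |
|---|---|---|---|---|
| 0.17 | 1.30 | 8.5% | 8.3% | 37% |
| 0.3 | 1.94 | 15.9% | 15.8% | 92% |
| 0.5 | 3.61 | 30.2% | 30% | about 100% |

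Simulations use gamma-Poisson counts, 23 against 23 clusters and equal populations. With no between-cluster variation, Poisson is valid (4.5% simulated in 4,000 runs).

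**If the switch is always made after a 5% dispersion test** (an assumed criterion), overall type I error is about 5 to 6.5% with quasi-Poisson scaling. With negative binomial it is somewhat higher: 5.6 to 8.0% for k from 0.17 to 1, in runs of only 500 per k.

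**If between-cluster variation is always allowed for.**
- Quasi-Poisson with t limits on 44 df: 4.7 to 5.2%.
- t-test on cluster rates: 4.3 to 5.5% over k = 0 to 1 (4,000 runs per k).
- Negative binomial with Wald limits: 5 to 7% over k = 0.17 to 1, from about 600 runs per k. The Monte Carlo error is √(0.05 × 0.95/600) = 0.9 percentage points, so the individual values are rough.

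**The case against.** **The written plan is Poisson with a fallback, not Poisson alone.** Where Poisson would be badly wrong, over-dispersion would be plain: the dispersion test triggers in 92% of trials at k = 0.3 and in nearly all at k = 0.5. This stands. A reader might infer from the table that the planned analysis has a 16 to 30% error rate. The documents do not support that, because those figures apply only if analysts see over-dispersion and keep Poisson. The test does miss mild over-dispersion, but there the unswitched error is only about 8%.

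**No k is planned.** A reader might take 0.17 as the protocol's value. It is derived, not stated. Sample size describes the outcome as binary, and on that basis with 40 people per cluster the count variance is (1 − 0.2625) × 1.39 = 1.03 times the mean, so plain Poisson gives about 5%. This also stands, and it is why the inflation is conditional on k. It does not rescue the default: the analysed counts come from whole catchment populations, where that binomial offset disappears.

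**Seroconversion outcomes.** Extending the inflation to SR_S and SR_H is tempting because the wording is the same. Those counts come from at most 40 sampled people per setting in each cluster, and no inflation has been computed for them.

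**The SAP will supply the detail.** A dispersion criterion or type of standard error could properly be left there, and scaled or robust errors are not excluded. But the protocol already names the default, excludes one alternative and makes the other optional. An SAP that follows it faithfully inherits the problem.

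**Conclusion.** The point holds in conditional form. The protocol fixes a primary model with no between-cluster variance, while assuming a non-zero ICC and expecting strong spatial variation, and nothing binding corrects this. If Poisson is kept, type I error is about 8%, 16% and 30% at assumed k of 0.17, 0.3 and 0.5. If the switch were mechanical, the excess would shrink to at most about 1.5 percentage points with quasi-Poisson scaling. The weakness is therefore mainly the discretion: the same data could be reported under either model, and only one of them is reliably near 5%. The figures rest on gamma-Poisson counts, equal catchment populations, 10.45 cases per cluster and a two-sided test.

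**What to change.** Replace the conditional rule with one analysis that applies whatever the dispersion looks like: quasi-Poisson regression of the 46 cluster counts on arm, with log person-time offset, a Pearson scale estimate and t-based limits on 44 degrees of freedom (43 if township is included). A t-test on cluster rates is an acceptable alternative. Name one of the two as primary.

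Negative binomial with Wald limits should not be treated as interchangeable, because it tends to stay slightly above 5% with this number of clusters.

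Use the same rule for SR_S and SR_H for consistency, without claiming a quantified error there.

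The cost is one sentence. If there is truly no over-dispersion, simulated power for a rate ratio of 0.70 is 92% (quasi-Poisson) or 93% (t-test) against 94% for Poisson. If the scale is not allowed to fall below 1, quasi-Poisson is then a little conservative (3.2 to 3.6%). At k = 0.17 power under the t-test is 88%, still above the stated 80%. It falls to 81% at k = 0.25 and 49% at k = 0.5, which is a consequence of real variation between clusters and not of the change in analysis.
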